## Methods and analysis

### Design

SHAPER-SO is a mixed-methods programme study, comprising quantitative and qualitative methods to assess the clinical and implementation outcomes outlined in the measures section below.

### Intervention

SO is a poststroke performance art intervention designed and delivered by the arts organisation Rosetta Life. This intervention initially developed and funded by King’s and Guy’s & St Thomas’ Charity, aims to improve recovery, agency and well-being after stroke.^14^

SO comprises three distinct stages (1) weekly workshops conducted over 12 weeks for stroke participants which will be facilitated by an integrated team of expert artists and ‘stroke ambassadors’ from the charity Rosetta Life, (2) a smaller group of ambassadors recruited from the workshops will be trained to become cofacilitators (ie, new stroke ambassadors), (3) a performance tour including education and taster workshops for audiences.

During sessions, which run for 3 hours each, participants devise a dance and music performance work from their own stories. The practice of ‘performing ourselves’ is key to achieving successful outcomes such as transforming the participants’ perception of identity. The culmination of the programme will be a public-facing performance to an audience of carers, healthcare practitioners, friends, family and the wider community.

Due to the ongoing COVID-19 pandemic and the necessity of shielding vulnerable adults and foreseeing increased anxiety in stroke survivors to attend in-person sessions, we have adapted the SO programme to be delivered through a mixture of live/face-to-face and online delivery (blended approach). Participants will be able to choose whether to attend the sessions/participate face-to-face or online based on their personal preferences and needs. The researcher will manage groups to ensure that all the participants who wish to attend in person will be able to do so during the 12 weeks.

The adapted programme will still be run in three stages, described below:

Stage (1): the workshops are the result of cocreation; the general framework is: weeks 1–3 building the performance company, weeks 4–6 devising the performance weeks 6–9 rehearsing the performance and weeks 10–12 are sometimes concertinaed into one production week introducing stage management, lighting and technical runs. Each of the 12 workshops contains a performance ‘class’ of 20–30 mins exploring movement and voice techniques and exercise.

Participants will be able to choose whether to attend the sessions/participate face-to-face or online based on their personal preferences and needs.

Stage (2): after the performance is completed, participants will be invited to a 4-day training programme where they will learn to act as advocates for life after stroke—termed ‘stroke ambassadors’. The optional ambassador training starts with an introduction to being an ambassador and an outline of the pathways available: (a) supporting artists in hospital and community contexts, (b) speaking the press and media/advocating for life after stroke, (c) engaging in academic research and (d) joining the steering group that informs activities and directions.

The skill development training is delivered in three stages: an introduction to movement practices and the traditions of independent dance, then an introduction to voice and improvisation and, finally, an introduction to performance. Each ambassador then constructs an individually tailored programme according to their personal goals and intentions in becoming an ambassador.

The programme will take place once weekly and will be led by a team of artists and supported by a leadership coach. All training will take place on Zoom until social distancing measures are lifted, and participants are willing to meet indoors—a blended ambassador training will be offered.

Stage (3): following training, a volunteer manager will coordinate a tailored programme where ambassadors support artists in recruitment, befriend the newly discharged stroke survivors and take part in small-scale performance tours to challenge the perception of disability. The tour will be delivered online with online screenings followed by a question and answers (Q&A) session with ambassadors, taster sessions and exercises delivered online with the ambassadors.

The programme will be delivered in two cycles of the complete three-stage intervention. At the end of the two cycles of the programme, a group of newly trained ambassadors will emerge. The programme seeks to develop a national network of ambassadors who will build capacity for performance arts in healthcare and a wider capacity for healthcare. The stroke ambassadors are graduates of the 12-week workshop that receive training, based on a leadership-coaching model, and they deliver a tailored advocacy programme according to their creative skills—befriending, performance administration and support, programme advocacy.

### Study setting

The study will take place online until conditions of the pandemic enable researchers, artists and participants to meet safely indoors, as per government guidelines. When it is feasible and safe to meet in person, participants, artists and researchers will meet in an established performance arts education centre to ensure that COVID-19 guidelines on cleanliness are guaranteed. When ran in person, the workshops are run in Central London locations, with a single centre running the programme in each cycle.

### Sample and recruitment

#### Stroke survivors

Consenting stroke participants will be included if they are:

over 18 years of age,have had one or more stroke(s),received inpatient care in a UK stroke care pathway,able to follow a two-stage command and hold a conversation in English if no supporter/friend is available to translate.

The following exclusion criteria will be applied to individuals:

with comorbidities that would prevent participation in group activities (eg, dementia or deteriorating or fluctuating palliative conditions),unable to understand English,unable to commit to the 12-week programme.

Additionally, stroke ambassadors will be included if they have been through the ambassador training and are involved in at least one programme cycle culminating in the tour.

All participants will be offered the option of completing an interview with their carer present. This will be offered both after the first 12-week programme and after the ambassador training, for those that wish to participate. Those that decline will be asked if they would be willing to provide their reasons why.

#### Wider stakeholder group

In addition to the stroke survivors that enrol on the SO programme, data will also be collected from a wider stakeholder group involved in the delivery or support of the programme. Individuals will be recruited if they meet the following criteria:

over 18 years of age,can hold a conversation in English if no supporter/friend is available to translate,can either be defined as a:Supporters: family members or carers.Deliverers: individuals responsible for the delivery of the research (facilitators and artists).Referrers: individuals involved in signposting (eg, doctors, nurses, healthcare workers).

Wider stakeholders will be excluded from participation if they are unable to understand English or if no supporter/friend is available to translate.

### Sampling

#### Sample size

We aim to recruit 75 new stroke survivors in total for the duration of the study. A prediction of 75 participants has been estimated based on the numbers that over the years running SO, *Rosetta Life* has been able to recruit in two consecutive cycles. This number has also considered the organisation being able to while maintain a manageable ratio of participants to artists and staff members, guaranteeing that SO is delivered to the highest standard.

Based on previous experience of running SO where participants then complete an ambassador training cycle, a drop-out rate of 20% is expected, and so the final number of ambassadors that complete the ambassador training is estimated to be 60.

The wider stakeholder group will be recruited from the network of people who are involved in the programme and present in the community. This includes the voluntary sector, health and social care sectors and clinical commissioners. A total of 47 stakeholders, a forecast based on the existing network numbers, will be recruited (12 carers, 10 clinical team members, 5 artists, 20 existing ambassadors).

### Recruitment procedure

Potential stroke survivor participants will be identified through signposting in community centres and care homes as well as engaging in presentations, screenings, taster sessions and performances during the tour.

Recruitment of potential participants will be done online. Screenings of performance extracts will be followed by taster sessions online and a Q&A with ambassadors. Potential participants will be directed to the project manager at Rosetta Life who will manage all referrals.

Potential participants will be offered a Participant Information Sheet (PIS) and an Informed Consent Form (ICF) and will be explained the details of the study. Written consent will be sought following a 48 hours colling-off period.

Wider stakeholders will be recruited from the networks of people involved in the referral, delivery or support of the programme.

A recruitment log will be kept by the research team to accurately record included and excluded participants as well as missing data from dropouts to account for possible sampling bias.

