**Trial registration number:**

NCT04864470.

Strengths and limitations of this studyThe first study examining an art intervention on stroke survivors, using a type 2 hybrid design, with a dual focus on effectiveness and implementation outcomes.The unique study design will result in a package of clinical and implementation data on this particular intervention.There may be inconsistency in participant experience throughout an intervention period if in-person sessions are switched online and vice versa due to COVID-19 social distancing restrictions.Access to the COVID-19-adapted online delivery of Stroke Odysseys may be challenging for people with severe acquired brain injury, resulting from stroke.

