### Outcomes

Data on the clinical outcomes will be collected from stroke survivors who have enrolled on the SO programme (see table 1). Data on the implementation outcomes will be collected from stroke survivors who have enrolled on the SO programme as well as the wider stakeholder group involved in the SO programme, including deliverers, referrers and supporters (see table 2).

Time points for data collection: T0—baseline; T1—midway through the 12-week programme (weeks 5–7); T2—immediately postperformance (12–14 weeks); T3—immediately after the advocacy training for stroke ambassadors.

To maximise inclusivity and outcome completion, and minimise participant burden, outcome assessments, where possible, will be conducted either face-to-face, online, by telephone or via postal questionnaire depending on the outcome measures being assessed, participants’ preferences and government COVID-19 guidelines.

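### Recruitment is stated as online, with no offline route or end date, although attendance and outcome collection are not restricted in this way; survivors without online access may be under-represented

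*Protocol article*

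**What the plan says.** Under Recruitment procedure, the protocol article first describes how people are found: "Potential stroke survivor participants will be identified through signposting in community centres and care homes", and also through tour events. It then sets the mode: "Recruitment of potential participants will be done online". The steps named are online: "Screenings of performance extracts will be followed by taster sessions online and a Q&A with ambassadors". After that, "Potential participants will be directed to the project manager at Rosetta Life who will manage all referrals", with no mode of contact given. The tour, a further source of recruits, is also remote: "The tour will be delivered online with online screenings followed by a question and answers (Q&A) session with ambassadors" (Intervention, stage 3).

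Other parts of the design are wider. On sessions, the Intervention section says: "Participants will be able to choose whether to attend the sessions/participate face-to-face or online based on their personal preferences and needs". Under Outcomes, assessments "will be conducted either face-to-face, online, by telephone or via postal questionnaire", where possible and depending on the measure, preference and guidance, with inclusivity given as one of the aims. The eligibility list under Sample and recruitment does not mention digital access. The limitations box concedes that access to the adapted online delivery "may be challenging for people with severe acquired brain injury".

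**The concern.** A survivor who cannot use online sessions is eligible, could attend in person once that is allowed, and could give outcomes by telephone or post. The recruitment step, as worded, offers that person no matching route.

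Survivors' implementation data come only from those who enrol (note to Table 2). Acceptability is the primary implementation objective, feasibility and appropriateness are secondary, and uptake is listed among the aims. If entry selects on ability to go online, all of these are measured in a group for whom the online part of a blended programme is easier than for eligible survivors at large. Demand for in-person places would likewise be observed mainly among people able to use the alternative. The wider SHAPER programme seeks to embed the interventions in healthcare and have them commissioned, so readers will want to generalise to stroke survivors broadly.

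**Working it through.** **Step 1: modes side by side (protocol article).**

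| Step | Section | Mode stated |
|---|---|---|
| Identification | Recruitment procedure | Signposting at community centres and care homes; tour events |
| Recruitment | Recruitment procedure | Online; online tasters; no alternative, no end date |
| Referral handling | Recruitment procedure | Project manager; mode not stated |
| Eligibility | Sample and recruitment | No digital-access criterion |
| Study setting | Study setting | Online until safe to meet indoors, then in person |
| Sessions | Intervention | Participant's choice of face-to-face or online |
| Outcomes | Outcomes | Face-to-face, online, telephone or post |

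The recruitment row is narrower than the eligibility, session and outcome rows. The study setting and the ambassador training each carry a clause that ends online working; the recruitment sentence does not.

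**Step 2: the plan's own figures.** The sample-size section reproduces: 75 × (1 − 0.20) = 60 ambassadors, and 12 + 10 + 5 + 20 = 47 stakeholders. No stated figure is wrong on this point. The issue is who enters, not how many.

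**Step 3: size of a possible bias.** Let q be the share of eligible, interested survivors missed because recruitment is online, and d the amount by which they would rate feasibility lower than those recruited.

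- Mean over all eligible survivors = (1 − q) × recruited mean + q × missed mean.
- Recruited mean minus that mean = q × d.

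The documents give neither q nor d, so both are assumptions:

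| q | d = 0 SD | d = 0.5 SD | d = 1.0 SD |
|---|---|---|---|
| 0.05 | 0 | 0.025 | 0.05 |
| 0.20 | 0 | 0.10 | 0.20 |
| 0.40 | 0 | 0.20 | 0.40 |

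The same on a proportion scale: suppose 80% of recruited survivors call the programme feasible, against a proportion p of those missed. The overstatement is q × (0.80 − p).

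- p = 0.80: 0, whatever q is.
- q = 0.20, p = 0.40: 0.20 × 0.40 = 0.08, or 8 percentage points.
- q = 0.40, p = 0.20: 0.40 × 0.60 = 0.24, or 24 percentage points.

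If the missed survivors would rate the programme higher, d is negative and the bias reverses.

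**The case against.** A reader might infer that survivors without online access can never enter. The text does not support that. Identification takes place at community centres and care homes, referrals go to a project manager by an unstated mode, and information and consent are not said to be handled online. Attending a taster is not an eligibility condition, and a supporter could help with access. These points stand: the barrier is probable, not absolute. They do not create an offline route, because the sentence on mode follows the signposting and is not qualified.

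Online working also has a stated reason. While meeting indoors is unsafe, the sessions are online too, so online recruitment matches delivery. This stands, and the mismatch matters mainly once in-person sessions run. It does not explain the absence of telephone and post, which are remote and already used for outcomes.

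A reader might also infer that the online-access limitation cannot appear in the data. That goes too far. Weekly attendance, drop-outs and their reasons are recorded, and deliverers, supporters and referrers rate feasibility and are interviewed about barriers. Someone who managed a single taster may still struggle over 12 weeks. The recruitment log is a further safeguard, intended to account for sampling bias, but it reliably captures only people who reach the team.

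Finally, a condensed article may leave contact logistics to the full protocol. That is fair for detail. Here, however, the article states a mode as a rule, and following that rule narrows entry.

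**Conclusion.** The point holds in limited form. Recruitment is stated as online, without an offline route or end date, in a design that otherwise allows in-person attendance and non-digital outcome collection and sets no digital-access criterion. This may under-represent survivors without online access and may bias the acceptability, feasibility and uptake findings.

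Upward is the more likely direction, but it is not shown: survivors who could attend only in person might rate that format as high or higher. It would therefore be wrong to conclude that feasibility is overstated. The size cannot be derived from the documents. The range of 0 to 0.40 SD, or 0 to 24 percentage points, rests wholly on assumed inputs and includes zero. This is a worthwhile, cheap improvement rather than an error that undermines the study.

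**What to change.** 1. Amend the recruitment sentence so that contact may be online, by telephone or by post from the signposting sites already in use, and in person when guidance permits. If offline contact is already intended, one clarifying sentence is enough.
2. Add inability to access online recruitment as a reason in the recruitment log, and ask the signposting sites to report such cases so that people who never reach the team are counted where possible.
3. If recruitment stays online, limit the feasibility and acceptability conclusions to survivors able to be recruited online.

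The cost is a wording change, one log code and slightly more administrator time. The intervention, sample size and analysis do not change. Selection at entry cannot be repaired after enrolment, so the change is best made before recruitment, or between the two cycles.

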### Study flowchart

A study overview is seen in the flowchart below (figure 1):

**Figure 1 F1:**
[figure not shown]
SHAPER-SO study flowchart. Scaling-up Health Arts Programmes: Implementation and Effectiveness Research-Stroke Odysseys.

### Data collection

This is a prospective mixed-methods study using a range of qualitative and quantitative methods at different time points pre, during and postintervention of each programme cycle.

Qualitative methods will comprise semistructured interviews and non-participant observations of training and production to assess experiences and attitudes towards the programme and its implementation.

Quantitative methods will be used to assess experiences and attitudes towards the SO programme and its implementation. Further information is included further in the ‘methods’ section in the outcome measures tables (tables 1 and 2) and the ‘assessment descriptions’ section.

**Table 1 T1:** Clinical outcomes

Objective	Clinical outcome measures/endpoints	Type of assessment	The time point for data collection
**Primary objective**			
**Secondary objectives**			
To study the context, mechanisms and interactions which take place during SO delivery	Non-participant observations of workshops	Qualitative	T1 (during workshop delivery)
To explore the learning and experiences of facilitators and participants	Semi-structured interviews- stroke participants and facilitators	Qualitative	T2
To explore stroke survivors’ preparation and participation in performances	Semi-structured interviews- stroke participants	Qualitative	T0

Data on the clinical outcomes will be collected from stroke survivors who have enrolled on the SO programme.

SO, Stroke Odysseys.

**Table 2 T2:** Implementation outcomes

Objective	Implementation outcome measures/endpoints	Type of assessment	Time points for data collection	Who data will be collected from

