**Methods and analysis:**

Scaling-up Health Arts Programmes: Implementation and Effectiveness Research (SHAPER)-SO aims to scale-up SO to 75 participants and 47 stakeholders, while simultaneously evaluating the effectiveness and implementation of the programme. The main research aim is to evaluate the implementation, effectiveness, impact and experiences of a community-based performance arts programme (SO for stroke survivors). This mixed-methods study will evaluate the experience and impact of SO on those participating using mixed methods (interviews, observations and surveys) before and after each stage and carry out non-participant observations during a percentage of the workshops, training and tour. Data will be analysed using quantitative and qualitative approaches. This is a study within the SHAPER programme.

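### The interview on taking part in performances is listed at baseline only, and no time point follows the stage 3 tour although the abstract promises data after every stage

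*Protocol article*

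**What the plan says.** **The performance row.** Under the secondary objectives of Table 1 (Clinical outcomes), one row concerns survivors' "preparation and participation in performances". The method is a semi-structured interview with stroke participants, and the only time point is T0. The Outcomes section defines T0 as baseline.

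**The other interview row.** Table 1 also has the row "To explore the learning and experiences of facilitators and participants", with interviews at T2. The Outcomes section places T2 directly after the performance, at 12 to 14 weeks.

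**The last time point.** The Outcomes section closes its list with "T3—immediately after the advocacy training for stroke ambassadors".

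**The order of stages.** Under Intervention, stage 1 ends in a performance. Stage 2 comes next: "after the performance is completed, participants will be invited to a 4-day training programme". Stage 3 follows the training, and in it ambassadors "take part in small-scale performance tours to challenge the perception of disability". The programme runs in two cycles, each containing all three stages.

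**What is promised.** The Methods and analysis paragraph of the abstract says that data will be collected "before and after each stage and carry out non-participant observations during a percentage of the workshops, training and tour". The semistructured interviews paragraph, under the assessment descriptions for clinical outcomes, adds interviews before and after programme cycles.

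**The concern.** Two parts of the schedule do not fit the objectives they serve.

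First, an interview held before the first workshop cannot cover participation in a performance. The Intervention section treats performing one's own story as central to how the programme is meant to work, so this is not a marginal objective. Staff who follow Table 1 literally would raise the topic at a visit where the participant has nothing to report but hopes and worries.

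Second, staff who follow the T0 to T3 schedule would stop collecting data before the tour begins. Nothing would then be gathered at a set time on acceptability, burden or unintended consequences among ambassadors who tour or befriend newly discharged survivors. Conclusions worded for the whole three-stage programme would rest mainly on two stages.

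**Working it through.** There is no sample size, power or event figure to reproduce. The check sets the order of the stages against the order of the time points.

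**Timeline, from Intervention and Outcomes**

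| Order | Event | Time point |
|---|---|---|
| 1 | Enrolment | T0, baseline |
| 2 | Stage 1 workshops: company building (weeks 1–3), devising (4–6), rehearsal (6–9), production (10–12) | T1, weeks 5–7 |
| 3 | Stage 1 performance | T2 directly afterwards, 12–14 weeks |
| 4 | Stage 2 ambassador training | T3 directly afterwards |
| 5 | Stage 3 tour and ambassador work | none |

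**Check 1: the performance row.** Its only time point is T0. Devising starts in week 4 at the earliest, so both preparation and performance come later. The row can capture expectations only.

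**Check 2: is the stage 1 performance followed by data?** Yes. Two of the four time points, T2 and T3, come after it. At T2, Table 1 has the interviews on learning and experience. At T2 and T3, Table 2 has the acceptability, appropriateness and feasibility scales, the EQ-5D and service-use schedule, and interviews on unintended consequences and on barriers and facilitators.

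**Check 3: is the stage 3 tour followed by data?** None of the four time points comes after it. Other parts of the article stop at the same place:
- The attendance register in Table 2 covers the 12-week programme and the ambassador programme.
- The survivor interview subsample is seen at T2 and T3.
- The implementation team's interviews with participants span the 12-week programme and the ambassador training.

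**Check 4: observation.** Table 1 lists workshop observation at T1. The ethnographic research paragraph covers a selection of the 12 workshops, including rehearsal and production, which run mostly after the T1 window. The Data collection section adds training and production. The tour is named as an object of observation only in the abstract.

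**Check 5: against the promises.** Collecting data around each stage requires a measurement after stage 3, and the schedule has none. Interviews after a cycle also imply interviews after the tour, because a cycle is defined as all three stages and the inclusion text for ambassadors describes a cycle as ending in the tour.

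**The case against.** The strongest reply is that much of this is already covered. T2 follows the performance and asks about experience, so a competent interviewer would raise performing there whatever the other row says. The T0 entry may simply be the planned pre-programme interview on concerns and expectations. For the tour, the abstract states observation, Data collection speaks of data after each cycle, and 20 existing ambassadors are among the stakeholders. Table 1 may also be incomplete as read, since its primary objective heading has no row beneath it. The flowchart is not shown, and an article condenses a fuller protocol.

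Part of this stands. A reader might infer that the performance is never assessed after it happens. T2 rules that out. A reader might also infer that observation is confined to T1, but the text on rehearsal, production and training says otherwise. Nor can one say that stage 3 is meant to yield no data at all, because observation of the tour is stated.

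The reply does not remove the two narrower points. A pre-programme interview could touch on plans for preparing at most, and the row also names participation. Existing ambassadors may speak of earlier tours, but nothing in the text directs the scales or interviews to the tour or times them after it. The flowchart might add timing, but the visible time-point list and tables would still disagree with the abstract.

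**Conclusion.** The point holds as an inconsistency in the schedule. One of the three secondary rows visible in Table 1 has a time point at which its objective cannot be met. One of the three stages has no time point after it, against a stated intention to collect data around each stage and after each cycle.

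It should be corrected, but it does not undermine the evaluation of stages 1 and 2. A reader might infer that the study can conclude nothing about the three-stage programme. That goes too far: this is a descriptive mixed-methods study with no powered endpoint, and tour observation, if carried out, would give some evidence on stage 3. What would lack support is a claim about stage 3 based on scales or interviews taken after it.

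The conclusion assumes that the T0 cell in Table 1 is complete as printed and that the flowchart adds no later time point. If a second entry was lost from that cell, the first part falls away. If the flowchart shows a contact after the tour, the Outcomes list and the tables still need to be brought into line with it.

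**What to change.** **Table 1.** Change the time point of the performance row to T0 (expectations) and T2 (experience of preparing and performing). T2 interviews with survivors are already planned, so this costs a table edit and an addition to the topic guide.

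**Stage 3.** Make the abstract, the Outcomes list, Tables 1 and 2 and the interview text agree, by one of two routes:
- Limit the evaluation claims and conclusions to stages 1 and 2 plus any tour observation, and state that interviews after a cycle mean those at T2 and T3. This needs no additional data collection but narrows what the study can say about the full programme.
- Add the promised tour observation to the schedule, together with a brief remote contact after the tour for touring ambassadors, for example the acceptability scale and interviews with a subset. The cost is a small extra data collection in each of the two cycles and some added burden on those ambassadors.
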